### Control selection

Control clusters (CONT) will be selected in locations with an incomplete sewerage sanitation system. Matching criteria for control clusters include: location in a geographic area that has similar environmental (elevation, hydrological data) and social (income, education, population density) characteristics to the intervention clusters; and at a distance of 1000 and 1500 m from the intervention cluster. Areas that received major infrastructure interventions and sanitation improvements in the last 5 years will be excluded from the selection frame for control clusters.

### Eligibility and enrolment

Before the recruitment of study participants, a census will be carried out within the selected eight clusters to enumerate all residents from households within <40 m distance from an open sewer. This would ensure that households and residents living in areas with a higher risk of leptospirosis transmission are included. At each census, the individual data (name, sex, age) and the geo-coordinates a primary household respondent would be collected. As a further step, we will randomly select population-based cohorts with 95 households (175 participants) per cluster. Residents will be eligible for inclusion in the study, if (1) they are 18 years of age or above, (2) have lived in the area for at least 6 months, (3) sleep in the household for at least three nights per week and (4) consent to the study procedures and complete an informed consent form. However, residents will be excluded if: (1) they do not meet all of the inclusion criteria; (2) they cannot provide written informed consent to participate in the study, (3) they refuse or are unable to provide demographic information and biological sample; (4) they are with limited mental health problems or other problems that have implications for survey responses or participation in any other phase of research activity.

For secondary outcomes we will include all children and young between 6 months and 17 years of age will be included in the study (online supplemental table 1). We will apply similar inclusion and exclusion criteria as described but excluding children for which their legal guardians do not provide written informed consent for their participation.

### Outcomes

#### Primary outcome measure

The study trial will consist of three specific phases: (1) baseline; (2) sanitation intervention implementation; (3) follow-up of the residents and evaluation of the sanitation intervention (figure 2). During the phase (1) a baseline survey will be conducted to characterise the demographics, SES and *Leptospira* seroprevalence in each cluster. During the phase (3) biannual serosurveys in the cohorts will be conducted to measure the primary outcome, *Leptospira* asymptomatic infection, and estimate the risk of infection during the dry and rainy seasons. The field team will collect blood samples from eligible participants with age ≥18 years. A blood sample (10 mL) will be collected from each study participant and examined for *Leptospira* antigen using the microscopic agglutination test diagnostic (MAT).^4^ MAT is the standard test to determine *Leptospira* infection in longitudinal studies and *Leptospira* infection will be defined as a fourfold rise in MAT titre or seroconversion (negative to ≥1:50) between samples from consecutive serosurveys. We will use a panel of six reference strains: representing *L. interrogans* serovars Autumnalis strain Akiyami A, Canicola strain H. Utrecht IV and Icterohaemorrhagiae strain RGA, *L. borgpetersenii* serovar Ballum strain MUS 127, *L. kirschneri* serovar Cynopteri strain 3522C and Grippothyphosa strain Duysterand the two clinical isolates: *L. interrogans* serovar Copenhageni strain Fiocruz L1-130 (isolated locally in 1996) and *L. santarosai* serogroup Shermani strain LV3954 (isolated locally). This procedure had the same performance in identifying MAT seroconversion in our prospective studies^4 14^ compared with the WHO recommended panel of 19 reference serovars. The screening will be performed with serum dilutions of 1:50–1:100. When agglutination is observed at 1:100, the sample will be titrated to determine the highest titre. As part of quality control procedures, two independent evaluations will be conducted for 8% of the samples and all samples from infected subjects.

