**Methods and analysis:**

This matched quasi-experimental study design using non-randomised intervention and control clusters was designed to assess the effectiveness of an urban simplified sewerage intervention in the low-income communities of Salvador, Brazil. The intervention consists of household-level piped sewerage connections and community engagement and public involvement activities. A cohort of 1400 adult participants will be recruited and grouped into eight clusters consisting of four matched intervention-control pairs with approximately 175 individuals in each cluster in baseline. The primary outcome is the seroincidence of *Leptospira* infection assessed through five serological measurements: one preintervention (baseline) and four postintervention. As a secondary outcome, we will assess *Leptospira* load in soil, before and after the intervention. We will also assess *Leptospira* exposures before and after the intervention, through transmission modelling, accounting for residents' movement, contact with flooding, contaminated soil and water, and rat infestation, to examine whether and how routes of exposure for *Leptospira* change following the introduction of sanitation.

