**Trial registration number:**

Brazilian Clinical Trials Registry (RBR-8cjjpgm).

STRENGTHS AND LIMITATIONS OF THIS STUDYThe first rigorous controlled intervention study for the effect of sanitation on *Leptospira* transmission in disadvantaged urban communities.This is a cluster-based non-randomised controlled trial with intervention clusters receiving a simplified sanitation intervention and matched control clusters no intervention.The alliance between the natural and social sciences and the potential that it has to deepen community perceptions about leptospirosis and interventions before and after, as well as involvement in it in some decision-making processes in the improvement of their health, well-being and sanitation.The allocation is non-randomised with selection based on intervention criteria determined by the implementer may have diluted intervention effects.Intervention will be carried out by the local public water and sanitation company, following their own planning, with no input or interference from the research team in the schedule or implementation.

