### Description of the sewerage intervention

During 2022 and 2023, the sewerage intervention (simplified sewerage intervention) will be implemented by the Public Water and Sanitation Bahia State Company (*Empresa Baiana de Águas e Saneamento*) in different urban locations in Salvador, Brazil. The expansion of the sanitation coverage in the city has generated an opportunity to assess the longitudinal effectiveness of the intervention on the transmission of sanitation-related diseases, such as leptospirosis. The company is government-owned, with responsibilities for managing, monitoring and distributing water and sanitation services throughout the state of Bahia. The costs, management and entire execution of the work will be the responsibility of the water and sanitation company, while the team of researchers will only monitor the development of the work.

This simplified sewerage intervention is characterised by receiving the sewage generated by a cluster of houses instead of individual houses. In conventional sewerage system designs, each household is connected directly to a principal line while in the sewer simplified system households are connected to branch lines within each block^23^ (online supplemental figure 1).

10.1136/bmjopen-2022-065009.supp1Supplementary data

The sanitation company will carry out the sewerage network works, which include the installation of a 150 mm primary pipe at the bottom of the residential lot, bordering a watercourse. Household sewerage networks are interconnected on one main line connecting to the main network, thus the intervention is expected to increase sanitation coverage in the study clusters by expanding the collection network. These interventions would exclusively be of a sewerage nature, with no complementary functions such as local drainage. Importantly, the intervention also includes community participation in the action designs and implementation.

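### As written, infections between the baseline and the first post-intervention survey count toward the primary outcome, although that interval contains the wait for works and the construction, which pulls the incidence rate ratio toward 1

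*Protocol article*

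**What the plan says.** - **Surveys.** The Abstract (Methods and analysis) says that seroincidence is "assessed through five serological measurements: one preintervention (baseline) and four postintervention".
- **Case rule.** Under Primary outcome measure, "infection will be defined as a fourfold rise in MAT titre or seroconversion (negative to ≥1:50) between samples from consecutive serosurveys". No interval is excepted.
- **Phases.** The same section orders the study as baseline, implementation, then follow-up, and adds: "During the phase (3) biannual serosurveys in the cohorts will be conducted to measure the primary outcome". It states no survey during implementation or at its end.
- **Works.** Under Description of the sewerage intervention: "During 2022 and 2023, the sewerage intervention (simplified sewerage intervention) will be implemented". The strengths and limitations box says that the company follows its own planning, "with no input or interference from the research team in the schedule or implementation".
- **Analysis.** Statistical analysis names quasi-Poisson regression for the incidence rate ratio, and mixed-effects logistic regression for infection risk. It gives no lag, washout or start of exposure. Limitations and bias adds a double difference of averages before and after the intervention.
- **Follow-up.** Study population and sample size gives 3 years after the intervention, plus a baseline before it.

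**The concern.** Five surveys form four consecutive pairs. The first pair joins a sample taken before the works to one taken after them. A resident of an intervention cluster who seroconverts while the sewer is still being awaited or built meets the case rule and counts against the intervention.

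Serology cannot date the infection within the interval, so such events cannot be sorted afterwards into before and after completion. The whole interval is either in the estimate or out of it.

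The stated aim is the effect of the sewerage on infection risk, and the power calculation uses reductions of 40%, 50% and 60%. Time before the sewer functions cannot carry that effect, so including it shrinks the estimate and usually the power as well. The article does separate before from after for rats and for the environmental variables, which are recorded before and at least 3 months after the intervention. The primary outcome has no such separation.

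**Working it through.** **The plan's own figure.** 8 clusters × 175 adults = 1400, as stated. The article gives neither power nor alpha, so the sample size cannot be reproduced as a power result.

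**Inputs from the article.** Effect sizes 40/50/60%; control rate 0.08 per person-year; 12% annual dropout; 3 years after the intervention; four matched pairs; between-cluster variation 0.03.

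**Assumptions.** Baseline to completion takes 0.5 to 2 years (not stated per cluster; the works run during 2022 and 2023). The arms have equal rates until completion, and the full effect holds from then on.

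**Scenario A: 3 years of follow-up after completion, with dropout.** Person-time up to T years is proportional to 1 − 0.88^T. For P years from baseline to completion, the share of person-time before completion is s = (1 − 0.88^P)/(1 − 0.88^(P+3)). The apparent reduction is (1 − s) × the true reduction.

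| P (years) | s | true 40% | true 50% | true 60% |
|---|---|---|---|---|
| 0.5 | 0.0619/0.3607 = 17% | 33% | 41% | 50% |
| 1 | 0.1200/0.4003 = 30% | 28% | 35% | 42% |
| 1.5 | 0.1745/0.4374 = 40% | 24% | 30% | 36% |
| 2 | 0.2256/0.4723 = 48% | 21% | 26% | 31% |

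**Scenario B: four six-monthly follow-up surveys.** These give three later intervals, 18 months in all. With no dropout and no effect in the whole first interval of L months, the apparent reduction is the true reduction × 18/(L + 18). A true 50% appears as 37.5% (L = 6), 30% (12), 25% (18) and 21% (24). A true 40% appears as 30%, 24%, 20% and 17%.

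Both scenarios are needed because four post-intervention surveys do not fill 3 years at two surveys a year, which would need six.

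**Sensitivity to risk during the works** (Scenario A, P = 1, true 50%).
- Works raise risk by 30%: rate ratio 0.30 × 1.3 + 0.70 × 0.5 = 0.74, an apparent reduction of 26%.
- A 25% reduction already holds before completion: 0.30 × 0.75 + 0.70 × 0.5 = 0.575, an apparent 42.5%.

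Both stay below 50%.

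**Power** (Scenario A, true 50%, two-sided alpha 0.05 assumed, 0.03 read as the coefficient of variation k). For four pairs, z_β = √{2(λ0 − λ1)² / [(λ0 + λ1)/Y + k²(λ0² + λ1²)]} − 1.96. Here λ0 = 0.08, λ1 is the control rate times the rate ratio, and Y is person-years per cluster. With cluster size 175, Y = 175 × (0.88^a − 0.88^b)/0.1278 for time a to b.

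| P (years) | first interval included | counted from completion | counted from a survey 6 months after completion |
|---|---|---|---|
| 0.5 | 82% | 90% | 83–84% |
| 1 | 71% | 89% | 81% |
| 1.5 | 60% | 87% | 79% |
| 2 | 51% | 84% | 76% |

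As an example for P = 1: Y is 548 with everything included, 384 from completion and 309 from six months later. The last column matches a risk period that starts at a survey after completion, where some exposed time is lost. At P = 0.5 the gain is negligible; at 1 year or more it is 10 points or more.

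The article labels 0.03 as both k and ICC. Read as an ICC (k about 0.59), power at 40/50/60% is only 12/18/25% even with no dilution and 3 years of person-time, so these power figures hold only under the first reading.

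**The case against.** **The quoted rule is a case definition, not a risk period.** It says what counts as an infection; a separate sentence assigns the measurement of the primary outcome to the phase 3 surveys, and the baseline is described as measuring seroprevalence. This is the best counter-argument, but it does not remove the interval. The first phase 3 survey yields incidence only against the baseline, and the Abstract lists the baseline among the five measurements of seroincidence. What stands is that the article never explicitly declares that it pools all intervals; the inclusion follows from reading the sections together.

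**Interval choice and lags belong in an analysis plan.** Often so, and one not shown may deal with them. The point here is that the outcome rule the article does fix takes in this interval, and nothing else in it offsets that.

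**The timing may be in the figures.** Figures 2 and 3 are not shown, and a note to Figure 3 ties later updates to the company's schedule. A reader might infer from the outside control of the works that the first interval is the longest and supplies most events. The text does not support this: it gives no duration per cluster, and 2022 to 2023 covers works in several parts of the city.

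**The size can be overstated.** This stands for Scenario B, which uses 18 months of later follow-up where the article states 3 years, and which gives the whole first interval no effect. Time between completion and the first survey is exposed and lessens the dilution.

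**A before-and-after analysis is already planned.** A reader might infer that the first interval can supply the before incidence for the double difference. It cannot do so cleanly. It includes construction, when risk may be altered: a raised risk would inflate the before value and exaggerate the benefit. It may also include time after completion, which would understate it.

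**Conclusion.** The point holds as one of structure and direction. As written, the first interval feeds the primary rate ratio and moves it toward 1 whenever the effect before completion is smaller than afterwards; added risk during construction moves it further the same way.

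The size is conditional. Under the article's own 3 years and 12% dropout, with no effect before completion and 0.5 to 2 years to reach it, a true 50% reduction appears as about 41% to 26%. The range of about 38% to 21% needs the shorter follow-up and no effect throughout the first interval, so it is the less favourable case and not the expected one. The documents do not show which applies, nor that the trial would miss a real effect.

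A related limit also stands: one pre-intervention survey gives seroprevalence only, so the double difference has no clean pre-intervention incidence for the primary outcome.

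**What to change.** 1. State that the primary-outcome risk period starts, in each matched pair, at the first survey after works are completed in the intervention cluster, and use the same calendar window for its control so that season and rainfall stay balanced.
2. Name the interval from baseline to that first survey a transition period. Report its incidence by arm separately, and include it in a sensitivity analysis of the rate ratio.
3. Do not use that interval as an unaffected before incidence. Say in Limitations and bias that one pre-intervention survey gives no clean pre-intervention incidence for the double difference on the primary outcome, and adjust for baseline seroprevalence instead.
4. Record the completion date for each cluster, and fix these rules before outcome data are analysed; a later choice of interval would be open to the data.

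**Cost.** Changes of wording and analysis, with no new samples. Three rather than four intervals inform the primary estimate, and exposed time between completion and the first survey is lost. If that survey comes long after completion the loss grows, and where the time to completion is short there may be little or no gain in power.

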#### Secondary outcomes

##### Environmental exposure secondary outcomes

Secondary outcomes for environmental effects will include microbiological assays to assess soil contamination with pathogenic *Leptospira*. The presence and concentration of pathogenic *Leptospira* will be evaluated in the eight clusters. Bases on prevalence the contamination soil with *Leptospira* in studies previous and packing density of 0.4 with minimum distances between collection points, a total of 68 soil samples and 15 water sewage samples will be collected in each cluster and transported refrigerated to the laboratory within 6 hours for processing. Sampling will take place in duplicate, with intervals of 7–9 days between them. After processing, soil and sewage samples will be stored at −80°C until molecular assays can be performed. The presence and concentration of pathogenic *Leptospira* will be evaluated using a qPCR assay (quantitative PCR), targeting the *lipL32* gene. Samples will be considered positive when the two qPCR replicates show amplification before a Cq of 40.^7^ Environmental variables for rainfall, temperature, landscape (remote sensing using drones), flooding and hydrological features will also be collected during rainy seasons before and at least 3 months immediately after the sewerage intervention.

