### Research aims and hypotheses

We hypothesise that the combination of a simplified sewerage infrastructure and community engagement activities will reduce the risk of *Leptospira* infection among disadvantaged urban communities in Salvador, Brazil. We further hypothesise that this approach will be effective in reducing: (1) frequency of human contact with open sewerage contaminated with pathogenic *Leptospira*; (2) rat infestation and (3) *Leptospira* load in the soil around the simplified sewerage. We aim to evaluate the efficacy of a sewerage intervention on reducing *Leptospira* infection and other health outcomes related to sanitation in disadvantaged urban communities in Brazil. Our specific objectives are to: (1) to evaluate prospectively the effectiveness of a simplified sewerage intervention in reducing the risk of *Leptospira* infection; (2) to determine the mechanisms by which the simplified sewerage reduce direct human contact with environmental pathogen load in urban slums. Figure 1 provides further details on our hypotheses concerning the effects of the sanitation intervention on the transmission mechanisms of urban leptospirosis. We conceptualise this protocol as focusing on the sanitation intervention to decrease leptospirosis; however, this study protocol generates rich opportunities to evaluate other health outcomes. Therefore, we additionally aim to investigate the effects of the sewerage intervention on childhood exposure to a range of enteropathogens, and long-term child neurodevelopment and anthropometry. As exploratory outcomes, we will also investigate the effect of the sewerage intervention on the reduction of risk of arbovirus infectious diseases.

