### Statistical analysis

Descriptive statistics will be employed to report the demographic, social, economic or environmental characteristics between the study clusters (intervention and control clusters). For the primary outcome, we will apply quasi-Poisson regression to estimate the incidence rate ratio of *Leptospira* infection. We will also evaluate the effect of the intervention on *Leptospira* infection risk using mixed-effects logistic regression models to account for clustering of the observations within study units and across repeated measures for individuals. We will model the overall effect of the intervention on infection risk while controlling for baseline sewerage and flooding exposure and potential confounding variables, such as age, sex, indicators of the socioeconomic level, and rainfall intensity during an annual period, which are presumably unrelated to the intervention (figure 1).

For the secondary outcome, we will conduct environmental analyses of *Leptospira* load between intervention and control clusters to compare environmental risk. To do this, we will model two leptospiral load outcomes, prevalence (binomial) and concentration (log-transformed), using generalised linear models with random effects to account for clustering within study units. The association between environmental contamination and hypothesised predictors of risk (rat abundance, human movement and ecological data) will also be explored in the model (figure 1).

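### Sewage-water samples are analysed only where sewage is present, so a post-works comparison of that component would understate removal of open sewage

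*Protocol article*

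**What the plan says.** Under *Environmental exposure secondary outcomes*, the sampling effort is the same everywhere: "a total of 68 soil samples and 15 water sewage samples will be collected in each cluster". The basis given is earlier data on soil contamination and a "packing density of 0.4 with minimum distances between collection points". On replication the text says: "Sampling will take place in duplicate, with intervals of 7–9 days between them". Samples are tested by qPCR for *lipL32*.

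Under *Statistical analysis*, the environmental comparison between intervention and control clusters has two outcomes: "we will model two leptospiral load outcomes, prevalence (binomial) and concentration (log-transformed"). No outcome is listed for the presence or extent of open sewage.

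Under *Description of the sewerage intervention*, "the intervention is expected to increase sanitation coverage in the study clusters by expanding the collection network". The first sub-hypothesis under *Research aims and hypotheses* is a reduction in "frequency of human contact with open sewerage contaminated with pathogenic" *Leptospira*. Objective 2 in the same section concerns how the works reduce contact with environmental pathogen load. The abstract names soil as the environmental outcome ("As a secondary outcome, we will assess *Leptospira* load in soil, before and after the intervention") and separately plans transmission modelling of exposures before and after the works, with contaminated water among them.

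**The concern.** Soil is still there after the works, so soil can be sampled in the same way before and after. Sewage water cannot, because it can be sampled only where it still lies in the open, and the works are designed to change exactly that. A prevalence and a log concentration calculated per sample obtained are therefore conditional on a state that the intervention alters.

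If much of the open sewage is piped but what remains is as contaminated as before, the sewage-water comparison would show little or no difference between arms. At stake is the sewage-water contribution to objective 2 and to the water input of the transmission model. The named soil outcome and the seroincidence outcome do not depend on it.

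**Working it through.** **The plan's own figure.** The number 15 cannot be reproduced. The article gives no prevalence, precision, power or minimum distance for it, and the stated basis refers to soil. As a plausibility check, take packing density = n·π·d²/(4A), with density 0.4 and A = 30,000 m² (the average cluster size of 0.03 km² under *Study settings*). Then d = 2·√(0.4·A/(n·π)):
- n = 68: d = 2·√(12,000/213.6) ≈ 15.0 m.
- n = 15: d = 2·√(12,000/47.1) ≈ 31.9 m.

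The first is a plausible soil grid. No distance is stated, so this neither confirms nor refutes either number. Nothing in it provides for sewage points that disappear.

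**Does it matter whether points are fixed or re-selected?** The article does not say which applies. Under the two stated outcomes the result is the same:
- *Re-selected:* the 15 are filled from sewage that remains, so every sample comes from a still-open stretch.
- *Fixed:* a point that has closed gives no water, hence no qPCR result and no log concentration. Unless a rule scores it, it drops out, and the analysis again covers only still-open points.

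**Size.** Let p be the positivity where sewage is present, equal in both arms at baseline. Let c be the share of intervention points that close, and r the factor by which positivity in the remaining sewage changes. Assume that no control point closes. The article gives none of these, so all are assumptions.
- Ratio among samples obtained: r·p / p = r.
- Ratio per baseline point, absence counted: r·p·(1 − c) / p = r·(1 − c).

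The two differ by the factor 1 − c, whatever p and r are. With r = 1:

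| Share closed (c) | Ratio, samples obtained | Ratio, per baseline point | Baseline points still open, of 15 |
|---|---|---|---|
| 50% | 1.0 | 0.50 | 7.5 |
| 80% | 1.0 | 0.20 | 3.0 |
| 95% | 1.0 | 0.05 | 0.75 |

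In counts, at p = 0.4 the expected positives among 15 samples obtained stay at 15 × 0.4 = 6.0. Per baseline point they fall to 3.0, 1.2 and 0.3. At p = 0.2 or 0.6 the starting count is 3 or 9, and the ratios do not change.

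**The case against.** The strongest reply is that the article describes no faulty sampling rule. It does not say that points are chosen anew after the works, that 15 must be reached in every round, or that a dry point is replaced. Fixed points with absence recorded fit the wording equally well. Sewage sampling after the works is only implied, since before-and-after is attached to soil load, to environmental variables and to the modelled exposures. Field procedures and coding rules normally sit in a full protocol or analysis plan, and neither is shown. All of this is correct. A reader might infer that field teams must go to stretches the works did not reach while controls keep their original points; the text supports neither statement. The point rests instead on the two outcomes that are stated, which have no value for absent sewage under either reading.

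Second, the named environmental outcome is soil load, and removal can be seen elsewhere: in movement data on proximity to open sewers, in diaries and retrospective mapping of contacts, and in drone, flooding and hydrological data. This stands, and it limits the point to the sewage-water component. Those sources do not measure pathogen load, however, and the article does not link them to the sewage-load model.

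Third, in a transmission model, load given presence is a legitimate input, with removal entering through contact. Scoring closed points as zero load there could count removal twice. This also stands and is reflected in the fix. It means one cannot say that objective 2 would necessarily get a wrong answer.

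Fourth, a reader might infer that a completely effective intervention would look ineffective. That does not follow: with all sewage piped there would be nothing to sample, and the missing samples would reveal it. Conversely, the works include no drainage function, so some surface water may remain at the original points.

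Last, the ratio of 1.0 follows from assuming unchanged load in the remaining sewage. That is so. The gap of 1 − c between the two measures does not depend on that assumption.

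**Conclusion.** The point holds for the sewage-water component alone. As the outcomes are stated, a post-works comparison would be conditional on sewage still being present and would understate a partly or largely effective intervention. The prevalence ratio it returns differs from the per-baseline-point ratio by the factor 1 − c. With 50% to 80% of points closed and load in the rest unchanged, that is 1.0 against 0.5 to 0.2. The closure share, the unchanged load and the absence of closure in controls are assumptions; the article gives no figures for them. Soil load and *Leptospira* seroincidence are unaffected. This is an avoidable weakness in one secondary measurement, with a cheap remedy, and it does not undermine the trial's main comparison.

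**What to change.** - Geo-reference the 15 sewage points in each cluster at baseline, before the works, since unrecorded points cannot be recovered later.
- Revisit the same points after the works in both arms, and record at each visit whether open sewage is present.
- Take as the sewage-water outcome, per baseline point, open sewage present and *lipL32*-positive. A point with no open sewage counts as not meeting it.
- Report prevalence and concentration among still-open points alongside, labelled as conditional on presence and descriptive.
- Enter presence of sewage and load given presence as separate inputs to the transmission model, so that removal is not counted twice.

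The cost is a field-procedure step and a change of outcome wording. No extra samples are needed, and fewer qPCR runs where points have closed. The downside is small: concentration will be available from fewer intervention points, for example about 3 of 15 per cluster if 80% close.
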